## Abstract

**Introduction:**

Rupture of an abdominal aortic aneurysm (rAAA) carries a considerable mortality rate and is often fatal. rAAA can be treated through open or endovascular surgical intervention and it is possible that more rapid access to definitive intervention might be a key aspect of improving mortality for rAAA. Diagnosis is not always straightforward with up to 42% of rAAA initially misdiagnosed, introducing potentially harmful delay. There is a need for an effective clinical decision support tool for accurate prehospital diagnosis and triage to enable transfer to an appropriate centre.

**Methods and analysis:**

Prospective multicentre observational study assessing the diagnostic accuracy of a prehospital smartphone triage tool for detection of rAAA. The study will be conducted across London in conjunction with London Ambulance Service (LAS). A logistic score predicting the risk of rAAA by assessing ten key parameters was developed and retrospectively validated through logistic regression analysis of ambulance records and Hospital Episode Statistics data for 2200 patients from 2005 to 2010. The triage tool is integrated into a secure mobile app for major smartphone platforms. Key parameters collected from the app will be retrospectively matched with final hospital discharge diagnosis for each patient encounter. The primary outcome is to assess the sensitivity, specificity and positive predictive value of the rAAA triage tool logistic score in prospective use as a mob app for prehospital ambulance clinicians. Data collection started in November 2014 and the study will recruit a minimum of 1150 non-consecutive patients over a time period of 2 years.

**Ethics and dissemination:**

Full ethical approval has been gained for this study. The results of this study will be disseminated in peer-reviewed publications, and international/national presentations.

**Trial registration number:**

CPMS 16459; pre-results.

Strengths and limitations of this studyProspective multicentre observational study across major city.Large number of patient cases in target population.Use of mobile technology to facilitate accurate data collection.Assessment and validation of clinical decision-making tool for prehospital diagnosis of ruptured abdominal aortic aneurysm.Potential for non-random patient selection and confounding introducing bias.Reliant on accurate documentation of final hospital discharge diagnosis for each patient encounter.Incomplete data entry sets are not saved.

## Background

Abdominal aortic aneurysms (AAAs) are a significant health problem that account for 4 deaths per 100 000 population per year.^1^ Rupture of an abdominal aortic aneurysm (rAAA) carries a high mortality rate and is often fatal.^2^
^3^ Although rare cases survive conservative management following ‘contained rupture’, survival from rAAA is generally only possible with definitive surgery, which can be either open repair or endovascular surgical intervention (EVAR). For patients with rAAA, many non-operative factors are key determinants of survival.^4^ The lowest mortality for rAAA is seen in hospitals that have greater bed capacities, greater availability of support services, higher annual procedural caseload of AAA repair with a greater proportion of cases undergoing endovascular repair.^4^ Data from a large prospective multicentre randomised clinical trial of different surgical techniques (IMPROVE) suggests that the type of surgery itself may not play as great a role in overall survival.^2^
^5^
^6^ In-hospital survival from rAAA, intervention rates and uptake of endovascular repair are lower in England than in the USA, further suggesting there is room for improvement in the organisation and delivery of care.

It is possible that more rapid access to specialist care might improve mortality for rAAA, though selection of the fittest patients for transfer precludes definitive evidence to support this likelihood.^7–11^ Currently in London, patients are taken to the nearest hospital regardless of its ability to provide repair for rAAA,^12^ and protocols for triage of suspected rAAA are not routine across the UK. Diagnosis is not always straightforward with up to 42% of rAAA initially misdiagnosed, introducing potentially harmful delay when patients require interhospital transfer.^13^ The signs and symptoms of rAAA may be unreliable and patients frequently show additional features that may confound the diagnosis.^14^ There is a need for an effective clinical decision support tool for accurate prehospital diagnosis and triage to enable transfer to an appropriate centre. Such triage systems are already in place for patients with suspected stroke, ST elevation myocardial infarction (STEMI) and major trauma which have all been shown to be effective in reducing morbidity and mortality.^15–17^ In London, patients with suspected rAAA are currently taken to the nearest hospital for further assessment, regardless of its capability to repair rAAA. This can introduce additional delays for patients who subsequently require transfer to a vascular service, which in turn might increase mortality. It is possible that rapid more accurate diagnostic assessment in the prehospital environment and direct transfer to a vascular centre capable of providing definitive intervention might permit reduced mortality for populations with rAAA. However, there are currently no clinical triage tools to act as decision aids for prehospital service providers to estimate the risk of rAAA diagnosis based on presenting symptoms and medical assessment. If rAAA could be more accurately diagnosed in the prehospital setting, there is potential that more patients might receive definitive care. Any such tool should be accurate and feasible for use in the prehospital setting.

FILTR is a pilot prospective multicentre observational study, assessing the diagnostic accuracy of an ambulance smartphone triage tool for detection of rAAA. The first stage in developing a prehospital triage system requires validation and assessment of a clinical decision support system. This will be conducted across London in conjunction with London Ambulance Service (LAS). LAS clinicians will use a logistic score developed at St George's Vascular Institute for use as a mobile app on a smartphone platform. During each patient encounter, key parameters required to predict risk of rAAA will be collected using the app. Final discharge diagnosis will be retrospectively identified and collated for each encounter. This will enable assessment of the feasibility, validity and safety of the prehospital smartphone triage tool for rAAA. Secondary analysis will also allow modelling of the implications of such an approach for ‘false positive’ patients with other differential diagnoses if transferred to a vascular centre, or the implications of such an approach for service configuration and workload.

## Methods

### Trial design and objectives

FILTR is a prospective multicentre observational study assessing the diagnostic accuracy of an ambulance smartphone triage tool for detection of rAAA for 2 years. The objective of FILTR is to assess whether a logistic score hosted on a smartphone app can be feasible and accurate for diagnosis of rAAA at the scene of an emergency.

### Ethical approval and dissemination

Full ethical approval has been gained from the NRES Committee North West, reference 14/NW/0123. Further consultation and approval has been obtained from the NHS Health Research Authority Confidentiality Advisory Group, reference: 15/CAG/0152. The results of this study will be disseminated in peer-reviewed publications and international/national presentations.

### Registration

This is a portfolio study with UK Clinical Research Network Study Portfolio no. UKCRN ID 16459.

### Inclusion criteria

All patients over the age of 18 years assessed by a LAS clinician with acute abdominal/back/chest pain or collapse requiring transfer to hospital who do not fulfil entry criteria for existing triage tools such as myocardial infarction (MI), stroke and major trauma during the recruitment period will be eligible for inclusion.

### Exclusion criteria

The exclusion criteria are:
Any patient under the age of 18 yearsAny patient not requiring transfer to hospitalAny patient with confirmed or suspected acute myocardial infarction (MI), major trauma or stroke as existing triage tools already exist for this condition

### Smartphone triage tool

St George's Vascular Institute and the London Ambulance Service have developed a scoring system to diagnose rAAA based on ten key parameters. The score was developed with logistic regression of ambulance records and Hospital Episode Statistics (HES) data for 2200 patients from 2005 to 2010. The score used routine ambulance clinician assessments and detected rAAA with 82.6% sensitivity (area under the receiver operating characteristic (ROC) curve 0.86). The parameters collected by the app are: age, gender, blood pressure, capillary refill time, temperature, and history of collapse, back pain, diabetes, cancer or peripheral vascular disease. This triage tool has been integrated into a secure mobile app available for smartphones on all major operating systems. This mobile app has been made available to all LAS clinicians for the observational study since November 2014. LAS clinicians, including paramedics, paramedic students and technicians, will download the app onto their own personal smartphone. A website was set up to coordinate educational meetings and provide regular study updates.^18^ LAS clinicians are advised to enter physiological parameter data as soon as it is safe to do so from a clinical perspective using the first available set of observations, and in the same circumstances as completing existing patient report forms (PRFs). Pilot results show that data entry takes an average (mean) of 16 s per patient. There will be no change to the underlying logistic regression model during the course of the study, and no intention to update or modify the app thereby preventing issues with version control. The app design prevents the saving of incomplete data entry at the point of care. Incomplete patient records will be included in the analysis, where possible as per the Strengthening the Reporting of Observational Studies in Epidemiology (STROBE) guidelines. There is the possibility for incomplete data in terms of diagnosis retrieval, outcome (mortality) retrieval and discordance between the PRF data and the app data. Owing to the study design, we will not be able to follow-up eligible patients whose data are not originally included in the app. This should not prove a limitation of the study as the aim of the study is to assess the sensitivity and specificity of the model for prediction of rAAA. Assessment of any incomplete data entries will provide an outcome measure regarding potential app user error rate. This will include a sensitivity analysis whereby the ROC curve for mortality and rAAA diagnosis using each combination of ‘app data’, ‘PRF data’ and ‘app/PRF concordant data’ will be produced.

### Primary outcome

To assess and validate the sensitivity and specificity of the rAAA smartphone triage tool

### Secondary outcomes

To assess feasibility and safety of a mobile app-based clinical decision support system delivered at the point of care in a pre-hospital setting. This includes cost-effectiveness, research effectiveness, paramedic satisfaction and overall utility.To model the financial effect and workload for LAS, emergency departments and tertiary vascular centres if the destination of a patient with suspected rAAA was determined by the smartphone triage tool, for example, the extra distance/time required for the ambulance to travel to a specialist hospital; or the modelled outcomes of care for ‘false positive’ patients without rAAA transferred for care at a vascular centre.

### Power calculation

Modelling from HES data covering the period 2005–2010 estimates that over a 12-month period 150 rAAA and over 1000 controls (ie, patients found not to have a rAAA) will be studied. The study will recruit a minimum of 1150 non-consecutive patients. Expected CIs associated with predicted model performance are as follows: 83% sensitivity (95% CI 75.9% to 88.2%); 73% specificity (95% CI 69.0% to 78.3%). The expected ROC curve characteristic will have an area under the curve statistic of 0.85±0.01.

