### Statistical analysis

True positive and true negative diagnoses will be defined according to the hospital discharge record retrieved by site investigators at each participating hospital. Contingency table analysis will allow reporting of sensitivity, specificity, positive predictive and negative predictive rates for the logistic score, with CIs determined by sample size. The development and validation data sets will be further explored for model refinement using a logistic regression approach, with the same entry variables entered into forward selection, removal from models at p<0.1, and significance ascribed at p<0.05. An ROC curve will be reported for rAAA diagnosis using the original logistic score, and the refined score at the study end. Separate logistic models will be designed to explore 30-day mortality. Where diagnosis or mortality data cannot be retrieved, ROC analysis is impossible. As per STROBE guidelines, this study will fully describe the available data for patients with diagnoses/mortality and those without diagnosis/mortality, and subject the demographics/presenting features of both cohorts to statistical comparison to explore whether the absence of diagnosis data has introduced selection bias to the study.

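### The expected 95% CI for specificity (69.0% to 78.3%) does not follow from 73% in 1000 controls; its width corresponds to roughly 345

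*Protocol article*

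**What the plan says.** The Power calculation section of the protocol article projects from historical hospital data that "150 rAAA and over 1000 controls (ie, patients found not to have a rAAA) will be studied" over 12 months. It then sets the size: "The study will recruit a minimum of 1150 non-consecutive patients". That minimum is 150 + 1000.

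The next sentence gives the expected confidence intervals for the predicted performance of the model: "83% sensitivity (95% CI 75.9% to 88.2%); 73% specificity (95% CI 69.0% to 78.3"%). The section gives no other control count and no interval method. The Statistical analysis section says the accuracy measures will be reported "with CIs determined by sample size".

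The primary outcome is sensitivity and specificity. These two intervals are therefore the stated precision for the primary outcome.

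**The concern.** Read in order, the section says that 150 cases give the sensitivity interval and at least 1000 controls give the specificity interval. Yet the specificity interval is 9.3 points wide. For a proportion near 73% that is too wide for 1000 observations. It is also lopsided in an unexpected direction, with 4.0 points below the estimate and 5.3 above.

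Specificity is half of the primary outcome. It also governs how many patients without a rupture would be sent to a vascular centre, which the Secondary outcomes section proposes to model. Per 1000 controls, the printed limits correspond to 217 to 310 false positives (1000 × (1 − 0.783) and 1000 × (1 − 0.690)). Limits of 70.2% to 75.7% correspond to 243 to 298. The sample size is described only through projected caseload and these expected intervals, so a reader cannot tell what precision the design delivers.

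**Working it through.** **Inputs**, from the Power calculation section unless noted:
- cases 150, controls 1000 (the stated lower bound), total 1150
- sensitivity 83%, printed CI 75.9 to 88.2 (the Smartphone triage tool section gives the development value as 82.6%)
- specificity 73%, printed CI 69.0 to 78.3

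**Step 1. Check the method on sensitivity (n = 150).**
- Wilson at 83%: 76.2 to 88.2. Exact (Clopper-Pearson) at 83%: 76.0 to 88.6. Wilson for 124/150: 75.8 to 87.9.
- None of these equals 75.9 to 88.2 to one decimal, but Wilson is within about 0.3 points at each limit.
- Sample size implied by the printed width of 12.3 points, using n = p(1−p) × (1.96 / half-width)²: 0.83 × 0.17 × (1.96/0.0615)² ≈ 143. This is close to the stated 150.

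**Step 2. Specificity with the stated controls (n = 1000).**
- Wald: standard error = √(0.73 × 0.27 / 1000) = 0.01404; half-width = 1.96 × 0.01404 = 0.0275.

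| Method, 730/1000 | 95% CI (%) | Width (points) |
|---|---|---|
| Wald | 70.25 to 75.75 | 5.50 |
| Wilson | 70.16 to 75.66 | 5.50 |
| Exact (Clopper-Pearson) | 70.13 to 75.73 | 5.60 |
| Printed | 69.0 to 78.3 | 9.3 |

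Ratio of half-widths: 4.65 / 2.75 = 1.69.

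**Step 3. Can anything rescue the printed interval at 1000 or more?**
- More controls only narrow it: at 1150 controls, Wilson gives 70.36 to 75.49.
- Moving the point estimate between 72.5% and 73.7%, with n from 1000 to 1150, never gives a width above 5.7 points.
- Raising the confidence level is not enough. At n = 1000 the Wald interval is 69.4 to 76.6 at 99% and 68.4 to 77.6 at 99.9%. Neither reaches 78.3.

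**Step 4. What sample size does the printed width imply?**
- n = 0.73 × 0.27 × (1.96/0.0465)² ≈ 350; with p = 0.74 it is about 342.
- A search over integer counts for limits of 69.0 and 78.3 to one decimal finds 254/345 and 257/349 (Wald), 252/341 and 255/345 (Wilson), and 268/363 and 271/367 (exact). Over all methods tried, the range is 340 to 368.

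**Step 5. Do the limits fit 73%?**
- Arms: 73 − 69.0 = 4.0 and 78.3 − 73 = 5.3. The midpoint is 73.65%.
- A Wald interval is symmetric. Wilson and exact intervals for a proportion above 0.5 have the longer arm below the estimate. The printed interval has the longer arm above.
- Even 345 controls at exactly 73% give a Wald interval of about 68.3 to 77.7 (half-width 1.96 × √(0.1971/345) = 0.0468). Every count that reproduces both limits has an estimate of 73.6% to 74.0%, which rounds to 74%.

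**The case against.** The strongest reply accepts the arithmetic and disputes how much follows from it.

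- *The figure of 345 is conjecture.* No count reproduces 73%, 69.0 and 78.3 together, so a mistyped limit, a truncated point estimate or another data source could explain the mismatch. This stands as a caution: 345 is a back-calculation that depends on method. It does not restore consistency with 1000 controls.
- *Sensitivity does not reproduce exactly either.* True, and it should be called approximate agreement. But the same width formula implies 143 against a stated 150 for sensitivity, and about 345 against at least 1000 for specificity. The two gaps are not comparable.
- *The interval may not be binomial.* The article names no method. A bootstrap or model-based interval, perhaps from the development data, could be asymmetric upwards. The objection to the asymmetry therefore holds only for standard single-proportion intervals. However, the text presents these as expected intervals directly after the planned sample and mentions no other source. If there is one, it needs stating.
- *The consequence is small.* The minimum of 1150 comes from projected caseload and was not solved from a target width. No decision rule uses 69.0 or 78.3, the workload modelling is not said to use this interval, and the final intervals will follow the achieved sample. If 1000 controls is right, the error is conservative. All of this is fair and limits the severity, but the stated precision for half of the primary outcome still contradicts the stated sample.

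**Conclusion.** The concern holds. With 73% specificity and 1000 controls, the 95% CI is about 70.2% to 75.7%, not 69.0% to 78.3%. The printed half-width is about 1.7 times the derived one. The printed width corresponds to about 345 controls (340 to 368 by method), and the limits are centred nearer 73.6% to 74% than 73%.

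This rests on a two-sided 95% interval for a single proportion with the stated controls as denominator, which is the natural reading of the section. The article does not settle which figure is wrong. If the control count is right, the design is more precise than claimed. If the interval is right, the total would be about 150 + 345 = 495, not 1150. The error affects the planning statement and does not alter conduct or the final analysis. It should be corrected, but it does not threaten the study.

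**What to change.** Reconcile the control count, point estimate and interval in the Power calculation section:

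- If 1000 controls is the intended denominator, state specificity as 73% (95% CI 70.2% to 75.7%, 1000 controls). Name the interval method and use the same one for sensitivity with its 150 cases.
- If the printed interval came from another data set or a different method, say so, give that control count and the matching point estimate, and correct the 1000 if it is not the number expected to be analysed. Report the precision expected from the planned sample alongside it.

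The cost is one corrected figure or one added denominator. Recruitment, data collection and analysis are unchanged.

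### The expected AUC of 0.85±0.01 does not follow from 150 rAAA and 1000 controls: as a 95% interval it is about 2.7 to 4 times too narrow, and ± is not defined

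*Protocol article*

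**What the plan says.** The Power calculation section of the protocol article uses Hospital Episode Statistics modelling to expect "over a 12-month period 150 rAAA and over 1000 controls", and adds: "The study will recruit a minimum of 1150 non-consecutive patients". The minimum is the sum of the two groups, 150 + 1000 = 1150.

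It then lists the expected performance with 95% confidence intervals: "83% sensitivity (95% CI 75.9% to 88.2%); 73% specificity (95% CI 69.0% to 78.3". The next sentence gives the AUC: "The expected ROC curve characteristic will have an area under the curve statistic of 0.85±0.01". The ± carries no label, no formula is given, and no larger number of cases is planned elsewhere in the article.

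For context, the Smartphone triage tool section reports that in the development data the score "detected rAAA with 82.6% sensitivity (area under the receiver operating characteristic (ROC) curve 0.86". The Statistical analysis section commits to an ROC curve for the original score and for a refined one. The Primary outcome section names sensitivity and specificity only.

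**The concern.** An AUC is driven mainly by the smaller group, here 150 cases. With that many cases an uncertainty of ±0.01 around 0.85 looks too small, whichever usual meaning ± has.

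The figure tells readers how closely the study will pin down discrimination. Taken as a 95% interval it promises 0.84 to 0.86. A validation AUC of 0.82 would then look like a clear fall from the expected 0.85, although by Hanley-McNeil it lies within sampling error of it. The same false precision would make a small gain from the refined score look more detectable than it is.

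**Working it through.** **Inputs.** All are from the Power calculation section: AUC A = 0.85; cases m = 150; controls n = 1000 (the stated floor); operating point 83% sensitivity and 73% specificity.

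**Is 150 the basis of the neighbouring figures?** For sensitivity, yes. With 124 of 150 detected (82.7%), the 95% interval is 75.8% to 87.9% (Wilson) or 76.0% to 88.1% (Jeffreys), against 75.9% to 88.2% stated. The specificity interval is wider than 1000 controls would give (Wilson 70.2% to 75.7%); its width fits about 350. Fewer controls would only make the AUC less precise, so n = 1000 is the more generous choice here.

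**Hanley-McNeil.**
- Q1 = A/(2−A) = 0.85/1.15 = 0.7391; Q2 = 2A²/(1+A) = 1.445/1.85 = 0.7811; A² = 0.7225.
- Var = [A(1−A) + (m−1)(Q1−A²) + (n−1)(Q2−A²)]/(mn)
- = [0.1275 + 149 × 0.01663 + 999 × 0.05858]/150,000 = [0.1275 + 2.478 + 58.522]/150,000 = 0.0004075.
- SE = 0.0202; 1.96 × SE = 0.040; interval about 0.81 to 0.89.

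**Binormal models.** Var = V_case/m + V_control/n, where each V is the variance of the placement values for that group (DeLong-type).
- Equal variances: both V = 0.0352. Var = 0.0352/150 + 0.0352/1000 = 0.000270; SE = 0.0164; half-width 0.032. A simulation gave SE 0.0165.
- Curve through 83%/73% with AUC 0.85: this needs a case/control SD ratio of about 0.66, with V_case = 0.0192 and V_control = 0.0554. Var = 0.0192/150 + 0.0554/1000 = 0.000183; SE = 0.0135; half-width 0.027.

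**Results against the stated 0.01.**

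| Method | SE, 150/1000 | 95% half-width, 150/1000 | SE, 300/2000 | 95% half-width, 300/2000 |
|---|---|---|---|---|
| Hanley-McNeil | 0.0202 | 0.040 | 0.0143 | 0.028 |
| Binormal, equal variances | 0.0164 | 0.032 | 0.0116 | 0.023 |
| Binormal through 83%/73% | 0.0135 | 0.027 | 0.0096 | 0.019 |

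The 300/2000 columns assume that the 12-month yield holds for both years of recruitment; the article does not plan on that number.

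**Other attempts to reach ±0.01.**
- Unlimited controls with 150 cases: Hanley-McNeil SE 0.0198; equal-variance binormal 0.0153.
- The development AUC of 0.86 in place of 0.85: Hanley-McNeil SE 0.0197.
- The most favourable model tried, SD ratio 0.5: half-width 0.024 at 150/1000 and 0.017 at 300/2000.

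**Cases needed for a 95% half-width of 0.01 at the same case mix.** Hanley-McNeil about 2,347; equal-variance binormal about 1,555; binormal through 83%/73% about 150 × (2.654)² = 1,056. That is roughly 7 to 16 times the planned 150.

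**The case against.** The strongest reply is that ± need not be a 95% half-width. The two preceding intervals are labelled as 95% CIs and the AUC is not; the change of notation may mean a standard error. Under a curve that fits the protocol's own operating point, the SE is 0.0135, which prints as 0.01 at two decimals. The equal-variance model, which gives 0.0164, fits that point less well: at 73% specificity it implies about 80% sensitivity, not 83%. Recruitment also runs for two years and 1150 is a minimum; at 300/2000 the same curve gives SE 0.0096. This stands in part. A reader might infer that ±0.01 is unattainable on any reading. The article does not support that, because a rounded SE under a favourable model comes close. It remains true that nothing in the text says SE, and that every method tried gives an SE above 0.01 at the planned 150/1000.

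A second reply is that little depends on the figure, and this stands. A reader might infer that the study is too small, or that its main result is overstated. The article supports neither: the primary outcome is sensitivity and specificity, no AUC threshold or AUC test is specified, and the final interval will come from the observed data.

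A third possibility is that ±0.01 was carried over from the development data. The article reports 2200 patients there but not the number with rAAA, so this cannot be checked, and the sentence is written as an expectation for this study.

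**Conclusion.** The concern holds in a limited form. The stated AUC precision does not follow from the plan's own inputs, and its meaning is left open.

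- **As a 95% interval:** about ±0.027 to ±0.040, so precision is overstated about 2.7 to 4 fold. This is firm: ±0.01 fails under every model tried, including at 300/2000.
- **As one SE:** about 0.014 to 0.020, so 0.01 is optimistic by about 1.4 to 2 fold. This is less firm, because the lower end depends on the score distribution and rounds to 0.01.

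The ranges assume an AUC of 0.85, 150 cases and 1000 controls, and span Hanley-McNeil and the two binormal models. The point should be fixed, but it changes neither the sample size nor the primary analysis.

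**What to change.** Say what ± denotes, name the method, and recompute the figure from the planned cases and controls. For example: with 150 rAAA and 1000 controls, an AUC of 0.85 is expected to have a standard error of 0.020 and a 95% CI of about 0.81 to 0.89 (Hanley-McNeil). If the authors prefer an equal-variance binormal calculation, the corresponding figures are 0.016 and about 0.82 to 0.88; the method should be named because the answers differ. If a larger two-year sample was intended, state those numbers and compute from them.

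The cost is one sentence. The only downside is a less favourable stated precision; no extra patients and no design change are needed.
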